## INTRODUCTION

1

Diabetes is a complex condition leading to disability and premature mortality with 7000 excess deaths in the United Kingdom in 2022.^1^ The International Diabetes Federation estimates 537 million people are living with diabetes globally^2^ of whom approximately 4.3 million reside in the United Kingdom.^3^ Over 90% have type 2 diabetes, with an increased prevalence in areas with high deprivation, poor healthcare access, poorer housing, reduced finances and lower educational attainment.^3^

Diabetes self‐management education (DSME), which includes support for healthy food and lifestyle choices, is fundamental to achieving good glycaemic control and is recommended internationally to help prevent diabetes‐related micro‐ and macrovascular complications.^4^, ^5^ Indeed, early delivery of DSME with timely pharmacotherapy may be particularly beneficial through the so‐called *legacy effect*.^6^, ^7^

Despite the National Institute for Health and Care Excellence (NICE),^5^ American Diabetes Association (ADA) and the European Association for the Study of Diabetes (EASD) stating that DSME is the foundation for successful diabetes management and prevention of metabolic comorbidities,^4^ the UK National Diabetes Audit suggests of 71% of people with type 2 diabetes offered DSME, only 7% attend.^8^

Approximately 20% of all UK hospital beds are currently occupied by people with diabetes and the number is expected to rise to 25% by 2030,^9^ most (92%) are admitted for other conditions and illnesses.^10^, ^11^

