### Data processing and analysis

3.4

To increase the efficiency of clinical trials researchers embarking on prospective longitudinal studies will often include restrictive eligibility criteria to restrict potential mortality from existing comorbid conditions.^22^ Such restrictions in retrospective studies limit generalisability of the findings and result in significant loss of individuals included in the study. An alternative approach introduced by Charlson^22^ classifies patients with comorbid disease according to their risk of death from disease at entry to a study, allowing researchers to classify the risk of one‐year and 10‐year mortality.^22^, ^31^ Charlson Comorbidity Index (CCI) can be classified as mild (1–2), moderate (3–4) and severe (≥5).^25^ With each increased level of the comorbidity index, there is a stepwise increase in the cumulative mortality attributable to comorbid disease.^22^ CCI will be calculated from CPRD Aurum to predict a patient's 10‐year risk of mortality and managed as a confounding factor during multivariate analysis.

Not all aspects of health data are captured in CPRD, for example, socio‐economic demographics which are an independent effect modifier contributing to increased mortality in people with type 2 diabetes, with mortality risk increased in those in the most deprived neighbourhoods by as much as 11% per quintile of deprivation where the person also had a diabetic foot ulcer.^32^ Linkage to patient level indices of multiple deprivation (IMD) deciles will overcome this. IMD will be managed as a cofounding factor during multivariate analysis and this limitation will need to be addressed fully in our discussion.

We will use primary care demographic data and READ codes for CPRD Aurum and laboratory tests to confirm main potential confounders at baseline. These include age, sex, time since first use of diagnosis code (as a proxy for diabetes duration and age at diagnosis in years), multimorbidity (CCI), BMI, smoking status and laboratory results for HbA1c, systolic blood pressure (SBP) and total cholesterol. Ethnicity and patient level IMD will be included following linkages with relevant health datasets.

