### Study size

3.5

The study sample includes all patients in CPRD Aurum available during the study period who meet the inclusion criteria. A feasibility search on Aurum identified people meeting the study inclusion criteria (*n* = 605 710). A priori calculation of the sample size whilst presenting some uncertainty cannot be determined beforehand as the sample size will be reduced by inclusion of confounding variables and exclusion of some individuals.^19^ The sample size included in this study from feasibility counts is far larger than usually considered in hypothesis testing situations such as those proposed in this study. This gives us confidence we have sufficient sample size in this study for a reliable assessment of the research questions. Nevertheless, as an example, the 21 398 ‘*ever*’ patients and 584 312 ‘*never*’ patients identified would be sufficient to detect a difference in the proportion hospitalised (main outcomes) of approximately 1.9% with a power of 80% and a significance level of 5%.

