### Statistical methods

3.6

Baseline characteristics of participants will be summarised using descriptive statistics (mean, median, interquartile range and standard deviations as appropriate). We will also summarise total number of hospital admissions and length of stay by age, age at time of diabetes diagnosis, diabetes duration, ethnicity and IMD decile.

The primary cohort is those who have ‘*ever*’ received DSME in each of the 10 years in the study to identify hospital admissions and cause of death during follow‐up. We will additionally have a matched diabetes cohort who have ‘*never’* received DSME to provide comparison (rate ratios).

An initial crude analysis will compare the proportion of hospitalisations and deaths between *ever* and *never* DSME groups. Chi‐squared tests will be used to compare these proportions. Similar tests will be used for subgroup analysis and alternative outcomes (cause‐specific hospitalisations and mortality).

Number of hospital admissions will be calculated to estimate relative risk of admissions and mortality by all‐cause and cause‐specific using a mixed Poisson model. Should the data be over dispersed a negative binomial mixed model will be adopted.

A Cox proportional‐hazards model will be used to measure time to event for first hospital admissions and mortality with the proportional hazards assumption checked using Kaplan—Meier curve plots and Schoenfeld residuals tests. If the proportional hazards assumption does not hold, then alternatives such as restricted mean survival times models will be used.

Baseline covariates will be reported among the ‘ever’ and ‘never’ groups, and a statistical test will be applied to see whether these differ significantly. These will be examined in multivariate models. We will address potential issues with confounding by indication firstly within the study design in which individuals in the ever group will be matched at baseline for age, sex, diabetes duration and age at diagnosis to individuals in the never group. All models will be adjusted a priori for CCI, IMD, HbA1c, BMI, smoking status, lipid level and SBP during multivariate analysis.

Statistical analysis will be conducted using R version 4.4.1. Alpha level will be set at 5% for statistical significance.

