### Limitations, generalisability and interpretation

4.1

The medical data available in CPRD are collected during clinical consultations rather than for research, thus the data may be limited by recording quality, and there may be variation in the consistency and accuracy of reporting and coding by GPs. This may introduce inaccuracy into the study findings.

Although CPRD data on diabetes diagnosis has a high level of completeness, not all patient groups or GP practices are captured, for example, private patients, prisoners or some residential home patients. Moreover, some patients chose to opt out of CPRD, and some are exception‐reported by GPs. Furthermore, CPRD data capture may be less complete for ethnicity and socio‐economic demographic data, but this can be largely overcome by data linkage.

This study is observational by nature and reverse causality cannot be excluded as a possible explanation for associations or inferences. We are reliant on the accuracy of ICD‐10 codes and SNOMED‐CT codes to define outcomes. These limitations may introduce bias to the study and will be fully acknowledged in the discussion. Although we will match groups at baseline and manage confounding a priori, potential residual confounding can never be completely eliminated, and causality would need to be confirmed in a randomised controlled trial.

This study has the potential to benefit patients by informing guidelines and clinical strategies for people living with type 2 diabetes.

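### Follow-up starts on the attender's DSME date, but neither the matching nor the fixed adjustment set includes recent hospital admissions, which the linked HES data can supply

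*Protocol article*

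**What the plan says.** - **Index date (Data selection, 3.3).** Baseline for an attender and for the matched controls is the date of the attender's DSME.
- **Matching (3.3, repeated in Statistical methods, 3.6).** Age, age at diagnosis, diabetes duration and sex. Section 3.6 presents this as the first defence against selection: "We will address potential issues with confounding by indication firstly within the study design".
- **Adjustment (3.6).** All models are adjusted a priori for CCI, IMD, HbA1c, BMI, smoking status, lipids and SBP. The confounder list in Data processing and analysis (3.4) adds ethnicity. Neither list mentions earlier admissions.
- **Source of comorbidity (3.4).** "CCI will be calculated from CPRD Aurum", that is, from the primary care record.
- **Linkage (3.4).** HES Admitted Patient Care data are linked. The only use described is to define admission outcomes.
- **Uptake (Introduction).** Of those "offered DSME, only 7% attend".
- **Limitations (4.1).** "reverse causality cannot be excluded as a possible explanation for associations or inferences". Residual confounding is conceded as well. No step to look for either is described.

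**The concern.** Day 0 is defined by something the attender did. A person who takes part in an education programme on a given date is, as a rule, not in hospital or acutely ill then. The control inherits the date without that filter and may be an inpatient, recently discharged or seriously unwell. If attenders had fewer recent admissions than controls, they would go on to have fewer admissions even if DSME did nothing.

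The planned covariates cover chronic disease and metabolic control better than current illness. CCI counts recorded diagnoses. HbA1c, lipids and SBP say little about admissions for other causes, and the Introduction puts 92% of admissions among people with diabetes in that category.

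The protocol recognises the mechanism in other people's work. In reviewing a cohort of older Argentinian patients, it attributes the higher mortality of non-attenders to their worse baseline state. There a 33% crude reduction in mortality became a weak 18% association after adjustment. Objectives 2 to 4 (admissions, mortality and MACE) face the same problem, and the results are meant to inform policy.

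**Working it through.** **The plan's own figure.** The protocol gives no estimate of this bias. Its only scale figure is in Study size (3.5): the cohort would be "sufficient to detect a difference in the proportion hospitalised (main outcomes) of approximately 1.9% with a power of 80" per cent. As an absolute difference this does not reproduce. With 21,398 and 584,312 patients, two-sided 5% (sidedness assumed) and 80% power, the smallest detectable difference is 0.58 points at 10% hospitalised and 0.98 at 50%. With 1:1 matching it is 0.80 to 1.35 points. The figure of 1.9 fits only as a relative difference at 50% hospitalised (1.95%). That is a separate matter. Here it shows that the study can detect differences of about one point, so a small bias matters.

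**Inputs.**
- From the documents: 21,298 attenders (Sample, 3.2; Study size prints 21,398, which changes nothing below). "Alpha level will be set at 5% for statistical significance".
- Assumed, not in the documents: share with an admission in the year before index, 18% vs 25% or 20% vs 24% (attenders vs controls); hazard ratio r of a prior admission for first admission, 1.5 to 3, remaining after all planned covariates; 1:1 matching; 30–50% hospitalised.

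**Step 1: apparent hazard ratio when DSME has no effect.**

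HR = [1 + p_ever(r − 1)] / [1 + p_never(r − 1)]

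| p_ever / p_never | r = 1.5 | r = 2 | r = 3 |
|---|---|---|---|
| 0.18 / 0.25 | 1.09/1.125 = 0.969 | 1.18/1.25 = 0.944 | 1.36/1.50 = 0.907 |
| 0.20 / 0.24 | 1.10/1.12 = 0.982 | 1.20/1.24 = 0.968 | 1.40/1.48 = 0.946 |

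On the log scale the distances from zero are 0.032, 0.058, 0.098 (first row) and 0.018, 0.033, 0.056 (second row).

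**Step 2: precision.** Half-width = 1.96 × √(2 / events per arm).
- 30% hospitalised: 21,298 × 0.30 = 6,389 events, half-width 0.035.
- 50% hospitalised: 21,298 × 0.50 = 10,649 events, half-width 0.027.
- If a quarter are complete cases the half-width doubles: 0.069 and 0.054.

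**Step 3: in how many of the six scenarios does the bias exceed the half-width?**

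| | 30% hospitalised | 50% hospitalised |
|---|---|---|
| Full sample | 3 of 6 | 5 of 6 |
| A quarter complete | 1 of 6 | 3 of 6 |

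**Step 4: the same on the risk scale.** With a recent admission in 15% of attenders and 20% of controls and r = 2 as a risk ratio, the apparent ratio is 1.15/1.20 = 0.958. The false difference is 30 × 0.042 = 1.25 points at 30% hospitalised and 50 × 0.042 = 2.1 points at 50%. The detectable differences are 0.89 and 0.98 points with the full counts, and about 1.23 and 1.35 points with 1:1 matching.

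**Limit of the calculation.** The formula holds the effect of a prior admission constant over follow-up of up to 10 years. If that effect fades, the bias in the average hazard ratio is smaller.

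**The case against.** The strongest reply is that much of the imbalance may already be handled, and that the rest cannot be sized.

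- **Other covariates.** Six variables besides CCI are in every model and will absorb part of the difference. This stands, though none measures recent admission.
- **Complete-case rule (3.7).** Patients without covariate records within 12 months of baseline drop out, which removes some controls who are out of contact with care. It does not remove those who are measured and unwell.
- **Twelve-month exclusion (3.2).** Admissions and deaths in the first 12 months after diagnosis are discarded in both groups. For patients attending soon after diagnosis this takes out part of the early period at risk of bias. It runs from diagnosis and not from the index date, so it does nothing for later attenders. The split is not given.
- **Selection is not absolute.** One might infer that every attender was by definition fit and out of hospital. Table 1 includes remote programmes, one coded merely as commenced, and the Discussion sets attendance at 10% engagement. Nor do low uptake (7%) and the 3.5% share of the cohort (21,398/605,710) prove selection on health; under-recording could contribute.
- **Existing checks.** One might infer that nothing in the plan could reveal the problem. Kaplan–Meier curves and Schoenfeld residuals could show an early, fading difference. They would not identify its cause, and the planned response, restricted mean survival time, does not address selection.
- **Longer confounder list.** Section 3.4 introduces its list as inclusive and 3.7 refers to a fuller one. Prior admissions may be on it; that cannot be known. The set in 3.6, however, is stated for all models without them.
- **Limitations and wording.** The objectives speak of association, and 4.1 says a randomised trial would be needed to confirm causality. That is fair, but it does not justify leaving out an available predictor of the main outcome.

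**Conclusion.** The point holds as a gap in a stated adjustment set. The index date selects attenders and not controls, and the matching and 3.6 covariates omit a direct predictor of the main outcome that the linked data can supply. Residual bias towards a DSME benefit is plausible.

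A reader might go further and conclude that a spurious benefit is likely. The documents do not support that: they give no prior-admission rates, no residual hazard ratio, no matching ratio and no hospitalisation proportion. Under the assumed inputs a null effect would appear as a hazard ratio of 0.98 to 0.91. At full size with 1:1 matching, the larger part of that range would reach nominal significance; with a quarter complete, only its upper end or upper half would.

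This should be changed before analysis. It does not invalidate the design.

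**What to change.** 1. In Statistical methods (3.6), add the number of HES Admitted Patient Care admissions in the 12 months before the index date (or at least any versus none) to the a priori adjustment set for all models. State that the 12-month-from-diagnosis exclusion applies to outcomes and does not remove admissions from this baseline count.
2. Report the ever/never admission rate ratio for that pre-index year beside the post-index ratio, as a diagnostic of baseline imbalance. Do not use it as a formal prior-event-rate-ratio correction, which is doubtful when earlier admissions influence attendance, and do not apply it to mortality, where no prior event can exist.
3. Exclude controls who are inpatients on the index date, at least as a sensitivity analysis. This does not reach people who are seriously ill at home.

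**Cost.** Protocol wording and a little analysis on data already linked. Patients without 12 months of HES coverage before index are lost; the documents do not allow that number to be estimated. Adjustment reduces self-selection but does not remove it, since motivation and engagement with care remain unmeasured.

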### Data selection

3.3

To minimise the impact of incorrect information or flawed subject selection the ‘*ever’* cohort will be matched at baseline to patients who have ‘*never’* received DSME (*n* = 584 312). Age,^22^, ^23^ age at diagnosis and diabetes duration^22^, ^24^, ^25^, ^26^ are the most important predictors of one‐year mortality in type 2 diabetes.^27^ Every decade of earlier diabetes diagnosis is associated with 3–4 years of lower life expectancy.^24^

Cohort analysis, systematic review and meta‐analysis have considered the association between diabetes and sex, demonstrating that women generally have a higher risk of coronary heart disease and all‐cause mortality (58%) compared to men and a 13%–17% greater risk of all‐cause mortality.^28^, ^29^ Moreover, the additional likelihood of developing cancer and the higher risk of premature mortality from having diabetes is more pronounced in women.^30^

Patients will therefore be matched at baseline for age ± 5 years, age at diagnosis ±5 years, diabetes duration ±1 year and sex who are present in the dataset from the same start year or earlier.

This study will adopt an intention‐to‐treat analysis, with patients contributing only to the original exposure group in which they have been assigned, irrespective of when they receive DSME. Baseline for the ‘ever’ group and their matched controls will be the date of DSME intervention. Patients will remain exposed until they are censored by death, leave the GP practice, leave a GP practice which contributes to CPRD data or end of the study period (29 March 2021).

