### Plans for addressing missing data

3.7

Assessment of data quality and completeness in CPRD Aurum suggests that correctness of type 2 diabetes is high (94%–98%) indicating that a diagnosis code if found is likely to be correct and there are likely very few patients with type 2 diabetes in the absence of a code.^37^ In our primary analysis, we will use a complete‐case approach based on the main potential confounders listed. We will conduct secondary analyses using complete cases for the full list of potential confounders, including those expected to have a high proportion of missing data which we do not expect to be missing at random.

CCI will be used to calculate an individual's 10‐year risk of mortality. As it cannot be assumed that covariate measurements (CCI, ever or never attended DSME, diagnostic codes) are missing at random we will not use multiple imputation for these measures.

Data will be recorded as missing where there is no record within 12 months of baseline. Depending on completeness of data a decision will be made on whether to use multiple imputation to manage covariates. As HbA1c, lipids and BP measures are amongst the nine key care processes^5^ completed within primary care every 12 months and linked to the GP Quality Outcome Framework, it is likely these are well completed with the dataset.

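### Baseline drug treatment is in neither the matching nor the a priori adjustment set, so any treatment difference left between attenders and controls is absorbed into the DSME estimate

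*Protocol article*

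**What the plan says.** Confounding is handled in two steps. Section 3.6 introduces the first with "We will address potential issues with confounding by indication firstly within the study design", meaning the matching. Section 3.3 gives its variables: "Patients will therefore be matched at baseline for age ± 5 years, age at diagnosis ±5 years, diabetes duration ±1 year and sex". The second step is regression, and Section 3.6 fixes its covariates for every model: "All models will be adjusted a priori for CCI, IMD, HbA1c, BMI, smoking status, lipid level and SBP during multivariate analysis".

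Section 3.4 lists the main potential confounders. Besides age, sex and time since diagnosis these include "multimorbidity (CCI), BMI, smoking status and laboratory results for HbA1c, systolic blood pressure (SBP) and total cholesterol", with ethnicity and deprivation added by linkage. Section 3.7 bases the primary complete-case analysis on the main confounders. It also mentions secondary analyses with "complete cases for the full list of potential confounders", but the article does not print that list.

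Baseline is one date per matched set: Section 3.3 says that for attenders and their "matched controls will be the date of DSME intervention".

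No section names glucose-lowering, lipid-lowering, antihypertensive or any other drug treatment as a matching variable, covariate, stratifier or sensitivity analysis. Treatment appears in the rationale only, where the Introduction says that "early delivery of DSME with timely pharmacotherapy may be particularly beneficial". Section 4.1 concedes residual confounding in general terms, without mentioning drugs.

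**The concern.** In a treated patient, HbA1c, systolic pressure and cholesterol are on-treatment values. Someone with an HbA1c of 55 mmol/mol on diet alone and someone with the same value on insulin carry the same covariate, although the second may have more advanced disease. The same holds for a blood pressure reached without drugs and one reached on several. Adjusting for the measured value therefore does not adjust for treatment stage. Diabetes duration within 1 year and the Charlson index capture only part of it.

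Treatment can relate to the outcomes in two ways. It can mark severity (insulin, for example), and it can protect (cardioprotective drugs, for example). If it also relates to attendance, the hazard and rate ratios for admissions, mortality and 3-point MACE mix education with treatment. In a cohort of this size, a small systematic shift may be as large as the random error around the estimate.

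**Working it through.** **Text check.** The plan gives no figure on this point, so the first check is of the lists.

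| Place | Variables | Drug treatment? |
|---|---|---|
| 3.3 matching | age, age at diagnosis, duration, sex | no |
| 3.4 main confounders | age, sex, time since diagnosis, CCI, BMI, smoking, HbA1c, SBP, total cholesterol, ethnicity, IMD | no |
| 3.6 a priori set, every model | CCI, IMD, HbA1c, BMI, smoking, lipid level, SBP | no |
| 3.7 wider list, secondary analyses | contents not given | unknown |

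**Possible size.** For an omitted binary treatment, the observed ratio is the true ratio multiplied by

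B = [1 + p_ever(RR − 1)] / [1 + p_never(RR − 1)]

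Here p_ever and p_never are the proportions treated in the two groups, and RR is the relative risk of the outcome for treated versus untreated patients. The relevant values are those that remain after matching and adjustment. The documents give none of them, so **all inputs below are assumptions**.

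*A drug class used by 40% of one group and 50% or 60% of the other:*

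| RR | 50% ever, 40% never | 60% ever, 40% never | 40% ever, 50% never | 40% ever, 60% never |
|---|---|---|---|---|
| 0.7 | 0.85/0.88 = 0.966 | 0.82/0.88 = 0.932 | 1.035 | 1.073 |
| 0.9 | 0.95/0.96 = 0.990 | 0.94/0.96 = 0.979 | 1.011 | 1.021 |
| 1.2 | 1.10/1.08 = 1.019 | 1.12/1.08 = 1.037 | 0.982 | 0.964 |
| 1.5 | 1.25/1.20 = 1.042 | 1.30/1.20 = 1.083 | 0.960 | 0.923 |

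The range is 0.92 to 1.08. The direction depends on which group is treated more and on whether treatment protects or marks severity.

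*Insulin as a severity marker, 10% of attenders:*

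| Never | RR | B | abs(log B) | B if the usage is swapped |
|---|---|---|---|---|
| 13% | 1.5 | 1.05/1.065 = 0.99 | 0.014 | 1.01 |
| 15% | 1.5 | 1.05/1.075 = 0.98 | 0.024 | 1.02 |
| 15% | 2 | 1.10/1.15 = 0.96 | 0.044 | 1.05 |
| 20% | 2 | 1.10/1.20 = 0.92 | 0.087 | 1.09 |

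**Random error for comparison.** Take the 21,398 attenders of Section 3.5 and assume 1:1 matching (the article states no ratio), no losses, and 30% to 70% admitted. The half-width of a 95% interval for a log ratio is about 1.96 × √(2 / events per group).

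- 30% admitted: events = 6,419; half-width = 1.96 × √(2/6,419) = 0.035.
- 70% admitted: events = 14,979; half-width = 1.96 × √(2/14,979) = 0.023.

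Of the four insulin scenarios, 0.014 is below this range, 0.024 is at its lower end, and 0.044 and 0.087 exceed it.

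The 1.9% detectable difference in Section 3.5 is not used as a yardstick. With the stated groups, two-sided 5% and 80% power, the detectable absolute difference is at most about 0.98 points (at a 50% base rate), so that figure does not reproduce as an absolute difference.

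**The case against.** The strongest reply is that the list may not be closed. Section 3.4 presents its confounders as examples, Section 3.7 refers to a fuller list, and an a priori set says what must enter, not that nothing else may. Covariate definitions and drug code lists commonly sit in a fuller document. This has some force: treatment may appear in the secondary analyses. It does not remove the point, because the set that Section 3.6 declares for every model, and the printed list behind the primary analysis, both omit treatment.

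Second, treatment may be a mediator. That is true of drugs started with or after DSME. The Introduction's remark on pharmacotherapy does not show that the groups differed in treatment beforehand. Treatment before the matched baseline date is not caused by that DSME attendance, so the objection limits the remedy but does not defeat it.

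Third, matching on duration and age at diagnosis, with adjustment for HbA1c and the Charlson index, already captures part of treatment stage. This stands: the residual imbalance may be smaller than assumed above.

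Fourth, a reader might infer that treatment differences will be credited to DSME as benefit, and in the same direction for every outcome. The documents do not support that. They report no treatment by attendance. A severity marker and a protective drug can pull in opposite directions, and the balance may differ between admissions and MACE.

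Finally, Section 4.1 already acknowledges residual confounding, but a general caveat does not replace a covariate that could be obtained.

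**Conclusion.** The omission is real in the stated primary models. Baseline treatment is neither matched nor adjusted for, and HbA1c, SBP and lipids enter without a treatment term. Whatever treatment difference remains between the groups is absorbed into the DSME estimate.

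Direction and size cannot be determined from the documents. The factor of roughly 0.92 to 1.08 illustrates assumed prevalences and relative risks and is not an estimate; swapping the most extreme insulin scenario gives 1.09. It can be comparable with random error for all-cause admissions, but the milder scenarios are not. The comparison also assumes 1:1 matching and full retention. Complete-case losses would widen the intervals, rarer cause-specific outcomes have wider intervals still, and more controls per attender would narrow them.

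This does not show that the study is biased towards DSME. It shows a gap in the adjustment set that is cheap to close.

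**What to change.** Add baseline treatment to the main confounders in Section 3.4 and to the a priori set in Section 3.6. Take it from primary-care prescriptions in a fixed window before the matched baseline date (6 to 12 months, for example), defined identically for attenders and controls:

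- glucose-lowering stage: none, non-insulin, insulin;
- statin: yes or no;
- antihypertensive or antiplatelet use: yes or no.

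State that drugs started after baseline are not adjusted for, because they may lie on the pathway from DSME to the outcome. Tabulating these variables by group at baseline would also show whether an imbalance exists.

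The cost is drug code lists, modest programming and possibly a minor update to the CPRD data specification, assuming that prescribing records can be supplied with the extract. No further patients are needed, and no figure in the article changes.
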